### *Secondary outcomes*

1. Admission to the Intensive Respiratory Care Unit , need of invasive/non-invasive mechanical ventilation, death secondary to COVID-19, proved via PCR-TR according to the OMS protocol.
2. Incidence and severity of adverse events  
Adverse event: all medical events in the subjects included in the trial. The adverse event doesn't necessarily need to have a causal relation with the studied treatment. Examples of adverse events include abnormal symptoms and signs, hypersensitivity reactions or alterations in laboratory samples.  
Severe adverse event: defined as an event that results in the subject's death, in an event that threatens life, that requires hospital admission or causes incapacity.  
Due to the known effects of HCQ, special attention will be given to the incidence of the following adverse events:
  - a) Cutaneous reaction, generally when used along other drugs.
  - b) Medullar suppression, which must be watched over monthly through a control blood count.
  - c) Severe hypoglycemia, in which case the treatment must be suspended.
  - d) Proximal myopathy with proximal weakness or muscular atrophy.
  - e) Increase of suicidal risk according to the C-SSRS scale.

Adverse reactions are defined as the answer to a compound that is harmful and involuntary, that occurs at doses that normally are administrated to human beings. The described adverse reactions are:

- 1- 10% ophthalmologic, dose dependent.
- 2- Non-defined frequency: dermatologic, endocrine, metabolic, gastrointestinal, hematologic, hepatic, central nervous system, immunologic.

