### **Specific objectives**

To compare the risk of symptomatic infection with COVID-19 in subjects treated with prophylaxis with hydroxychloroquine against the risk of symptomatic infection with COVID-19 in subjects treated with placebo.

To estimate the risk of presenting the composite outcome (admission to intensive respiratory care unit, need of mechanical invasive /non-invasive ventilation and death) among subjects with high exposure to COVID-19, treated with prophylaxis with HCQ against those treated with placebo.

To estimate the risk of adverse effects in healthcare workers treated with prophylaxis with hydroxychloroquine against the risk of adverse effects in subjects treated with placebo.

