### *Main outcome*

Symptomatic infection (dry cough with or without dyspnea, with or without fever) due to COVID-19 proved via PCR-TR according to the OMS protocol.

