### *Final calculation*

According to the proposed statistical analysis, the difference in time to outcome will be performed with a log-rank test, using the following formulas:

$$n = \frac{d}{2 - S1(\infty) - S2(\infty)} \text{ y } d = (Z\alpha(2) - Z1 - \beta)^2$$

Considering a difference of 10% of higher survival rates free of COVID-19 and considering a reported survival rate free of COVID-19 of 76%, a sample size of 159 per group is obtained. Considering the losses, it is decided that 200 subjects will be included per group, for a total of 400 subjects.

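### The adverse-event outcome also counts the COVID-19 efficacy events, so the overall adverse-event comparison nets drug harm against infection benefit

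*Protocol*

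**What the plan says.** The protocol's Secondary outcomes section lists the incidence and severity of adverse events as the second secondary outcome. It defines the term broadly: "Adverse event: all medical events in the subjects included in the trial". It adds that "The adverse event doesn't necessarily need to have a causal relation with the studied treatment", and that "Examples of adverse events include abnormal symptoms and signs, hypersensitivity reactions or alterations in laboratory samples". The severe class is "defined as an event that results in the subject's death, in an event that threatens life, that requires hospital admission or causes incapacity".

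The efficacy outcomes sit beside this. The Main outcome is "Symptomatic infection (dry cough with or without dyspnea, with or without fever) due to COVID-19 proved via PCR-TR". Secondary outcome 1 is intensive respiratory care admission, ventilation or death due to PCR-proven COVID-19. No section takes these events out of the adverse-event count.

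The third Specific objective, with placebo as the comparator, opens "To estimate the risk of adverse effects in healthcare workers treated with prophylaxis with hydroxychloroquine against the risk of adverse effects in subjects treated with". Statistical analysis applies a hazard ratio with a 95% confidence interval to the main and the secondary outcomes alike. Ethical considerations expects the two effects to run in opposite directions on hydroxychloroquine: less symptomatic COVID-19 and more adverse events from the prophylaxis.

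**The concern.** A symptomatic, PCR-proven infection is a medical event with abnormal symptoms, so it meets the adverse-event definition. A COVID-19 intensive-care admission, ventilation or death meets the severe definition. The same cases then enter the efficacy comparison and the overall safety comparison.

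If the drug prevents infections, the placebo arm collects extra adverse events that have nothing to do with tolerability. The overall between-arm difference becomes harm minus benefit. It understates toxicity most when efficacy looks best, which is also when the Experimental group section contemplates unblinding and offering prophylaxis to both arms. The safety objective asks about harm from the drug, and the overall count as defined does not isolate it.

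**Working it through.** The protocol gives no expected adverse-event rate or adverse-event comparison, so there is no figure of its own to reproduce. The calculated sample size of 159 per group is not an input here.

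**Inputs**
- COVID-19-free proportion on placebo: 76% (Final calculation), so 1 − 0.76 = 24% infected.
- Planned effect: "Considering a difference of 10% of higher survival rates free of COVID-19", read as 10 percentage points, so 86% COVID-19-free and 14% infected on hydroxychloroquine.
- Participants per arm: 200 (Final calculation).
- Background adverse-event rate *b* and drug-caused rate *t*: not given. Assumed ranges are *b* = 0 to 40% and *t* = 5 to 20%.
- Background events, infection and toxicity are taken as independent.

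**Infections counted as adverse events.** Placebo: 0.24 × 200 = 48. Hydroxychloroquine: 0.14 × 200 = 28. That is 20 fewer on the drug. Where *b* or *t* is above zero, some of these participants would also have another adverse event.

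**Proportion with any adverse event**
- Placebo: 1 − (1 − *b*)(0.76)
- Hydroxychloroquine: 1 − (1 − *b*)(0.86)(1 − *t*)
- Difference, drug minus placebo: (1 − *b*)[0.76 − 0.86(1 − *t*)]
- Difference with COVID-19 removed: (1 − *b*)*t*

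**Break-even.** The difference is zero when 1 − *t* = 0.76/0.86, so *t* = 1 − 0.8837 = 11.6%, whatever *b* is. Below that toxicity the drug arm shows fewer participants with an adverse event than placebo.

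**Range.** Differences are in percentage points. Power is for a two-proportion comparison at two-sided 5% with 200 per arm. Each cell runs from *b* = 0 to *b* = 40%.

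| *t* | COVID-19 counted | Power | COVID-19 removed | Power |
|---|---|---|---|---|
| 5% | −5.7 to −3.4 | wrong direction | +5.0 to +3.0 | 90% to 9% |
| 10% | −1.4 to −0.8 | wrong direction | +10.0 to +6.0 | over 99% to 23% |
| 15% | +2.9 to +1.7 | 10% to 5% | +15.0 to +9.0 | about 100% to 44% |
| 20% | +7.2 to +4.3 | 36% to 14% | +20.0 to +12.0 | about 100% to 67% |

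Example with *b* = 30%, *t* = 10%: placebo 1 − 0.70 × 0.76 = 46.8%; drug 1 − 0.70 × 0.86 × 0.90 = 45.8%; difference −1.0. With COVID-19 removed: 30% against 1 − 0.70 × 0.90 = 37%, difference +7.

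**On the hazard scale.** The protocol names hazard ratios, and for time to first adverse event the cause-specific hazards add. The cumulative infection hazards are −ln 0.76 = 0.274 on placebo and −ln 0.86 = 0.151 on the drug, a gap of 0.124. Toxicity at break-even has cumulative hazard −ln(0.8837) = 0.124. If the sources share a time course, the hazard ratio is 1 at the same 11.6%.

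**Severe adverse events.** The direction is the same wherever the drug prevents severe COVID-19, but the protocol gives no rates from which to size it.

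**The case against.** The strongest reply is that a definition independent of causality is a capture rule: it says what to record, not which contrast to report. How to tabulate events is commonly left to a statistical analysis plan, which may exist and is not shown. The split is also possible at analysis, because symptomatic participants are tested for SARS-CoV-2 (Tests to perform). This largely stands and is why the point is minor. What remains is that the protocol names the overall incidence as a secondary outcome, defines it to include the efficacy events and applies the hazard ratio to it.

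The protocol also separates drug harm in several places. Secondary outcomes picks out five known toxicities for their own incidence and defines adverse reactions as harm from the compound. Gradation of adverse reactions words grades 1 to 3 as effects of the compound, sets ECG and laboratory criteria, and lists COVID-19 symptoms alongside adverse events in the weekly enquiry. This stands: fewer infections would largely leave those comparisons alone. The protocol does not say, however, which of these sets answers the safety objective.

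Four stronger readings are tempting and are not supported.
- A reader might infer that toxicity would be hidden from the trial as a whole. Only the aggregate adverse and severe adverse event counts are affected.
- A reader might infer that the monitoring committee would be misled by its tables. No such tables are described. The committee section gives members the data and the randomization list, with which they can separate infections from other events.
- A reader might take 10% as the true toxicity, from the ophthalmologic entry in Secondary outcomes. That line is garbled and could be a list number or a range, and Justification calls the retinal risk at the trial dose minimal. The 10% row above is only an illustration.
- A reader might conclude that COVID-19 and all its complications should simply be excluded. PCR shows infection; it cannot say whether a raised transaminase or a long QT in an infected participant comes from virus or drug. Exclusion would also drop ward admissions that secondary outcome 1 does not count, and could conceal harm if the drug made infection worse.

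**Conclusion.** The point holds as a minor one. As written, the overall adverse-event and severe-adverse-event outcomes include the efficacy events. At the planned 24% against 14%, the infection benefit offsets drug toxicity in up to about 11.6% of participants in the any-adverse-event comparison. That threshold rests on the planning rates, on reading the 10% as percentage points and on independence; it does not depend on the background rate. Any particular between-arm difference depends on background and toxicity rates that the protocol does not supply. At an interim look with fewer infections accrued, the offset would be smaller. For severe events only the direction can be stated.

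**What to change.** Add a sentence to Secondary outcomes: the between-arm incidence of adverse events and of severe adverse events will be reported side by side in two versions, with and without the PCR-confirmed COVID-19 events already counted in the main outcome and secondary outcome 1, and both versions will go to the monitoring committee.

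Remove events, not participants, so that someone with COVID-19 and a separate event still counts for the latter. Keep laboratory and ECG abnormalities, and hospital admissions not counted in secondary outcome 1, in both versions. No causal adjudication is then needed, and harm from a worsened infection stays visible.

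The cost is one extra table and no new data. The reduced version is not a pure measure of toxicity, since some abnormalities due to infection remain in it, so it must be read beside the full one.

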## **Background**

The outbreak of respiratory infections due to coronavirus 2019 (COVID-19) began in China in December 2019, in the city of Wuhan, Hubei province (1 – 5). From this city, the outbreak has extended to other Chinese provinces and other countries (6). Until February 16, 2020, 28 countries had recognized confirmed cases, with 70,548 infections and 1,770 deaths in China and 413 infections in Japan (6). As other coronavirus, like SARS and MERS, the original human infection probably came from contact with animals, but effective transmission between humans has been proved, with a growth rate higher than 1 estimated at 2.6 (7) and a rapid duplication of cases that guarantees not only the continuation of the epidemics but its expansion, as has been observed so far.

COVID-19 has a wide range of clinical presentations, from asymptomatic infections to fatal disease with severe lung damage, respiratory failure and multiorgan failure. Severe damage has been associated, as in severe influenza, to a systemic

inflammatory reaction or cytokine storm, that may be attenuated by the immunomodulator effect of chloroquine or hydroxychloroquine. The fatality rate of COVID-19 has been estimated around 2%, but in severe cases with respiratory failure or need of intensive care it is considerably higher, between 10 – 15%, and could easily go up to 20 – 30% depending on the criteria of admission to an intensive respiratory care unit.

Until now there is no effective treatment for COVID-19 available, but it was recently reported that Remdesivir and chloroquine are effective in vitro. This one, in concentrations that can be obtained in vivo (8). Chloroquine and hydroxychloroquine (HCQ) are originally antimalarial drugs, almost identical chemically, that have been in regular use for decades, with a good security profile and accessible cost. The main toxicity of HCQ, investigational drug in this trial; is retinopathy, being its main associated risk factors doses higher than 5 mg/kg weight/day, lengthy use (longer than 10 years) and history of kidney failure, as well as use of tamoxifen. Other adverse effects reported with HCQ, happening scarcely, are alterations of heart conduction, cardiomyopathies, neurological symptoms such as nystagmus, headache, insomnia and nightmares, among others.

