## **Justification**

There is a lack of an approved pharmacologic treatment for chemoprophylaxis of COVID-19 and based on the in vitro effectivity of HCQ against the SARS-CoV-2 virus, its security profile and low cost we propose a randomized double blind controlled trial to evaluate the efficacy and security of HCQ to prevent symptomatic and severe infections in the healthcare workers highly exposed to COVID-19. The proposed dosage for prophylaxis is 200 mg/day. This is lower than 5 mg/kg/day in subjects who weight more than 50 kg, which makes the risk of retinal toxicity minimal, since subjects who weigh less than 50 kg will be excluded. In case of proving that the incidence of symptomatic and severe COVID-19 in health workers diminish significantly, this prophylaxis strategy may be one of the best tools to upkeep the security of the healthcare personnel exposed to COVID-19.

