### *Gradation of adverse reactions*

Grade 1: mild adverse event: refers to the effects that may happen due to the compound that are temporal and don't cause permanent harm or incapacity.

Grade 2: moderate adverse event; refers to the effects that may happen due to the compound that are temporal but require support from other therapeutics to be corrected and don't cause permanent harm or incapacity.

Grade 3: severe adverse event; refers to the effects that may happen due to the compound that might be temporal or permanent, without risk of mortality or incapacity.

Grade 4: adverse advent with risk of death or incapacity.

Evaluated through the following study:

Electrocardiogram: QT interval prolongation.

Blood count: bone medulla suppression, defined with the following values: neutrophiles < 500/microliters, platelets < 20,000/microliter, reticulocytes < 20,000 / microliter.

Hepatic failure: INR > 1.4, ALT > 33 units/liter, AST > 55 units/liter, total bilirubin > 4 mg/dl, platelets < 150,000/microliter.

Due to the nature of the study, having a captive population that comes to the INER at least five days a week, it is possible to estimate the number of days to the outcome. All participants will be instructed to notify the researchers in case of presenting cough, dyspnea or any other new sign or symptom. Weekly researchers will ask all included subjects about the symptoms associated with COVID-19, as well as any possible adverse events.

If any study subject presents adverse reactions, the treatment will begin immediately, and it will be notified at the same time. The initial treatment will be administered at the INER, support from other institutions will be requested, if necessary, without cost for the subject.

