#### *Exclusion criteria*

- Known hypersensitivity to HCQ, evidenced by anaphylaxis.
- Current treatment with HCQ or chloroquine.
- Weight less than 50 kg at the basal evaluation.
- Women with last menstrual date a month before recruitment without a pregnancy test.
- Women with positive pregnancy test.
- Lactating women.
- History of chronic hepatic disease (Child-Pugh B or C)
- History of chronic kidney disease (GFR lower or equal to 30)
- History of treatment with tamoxifen.
- History of retinopathy of any cause, and/or loss of central vision, loss of nocturnal visual acuity, blurred vision and alteration of color vision.

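### Eye events, which the protocol itself names as the drug's main toxicity, are missing from the special-attention list, and no eye-specific question follows the entry exclusion

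*Protocol*

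**What the plan says.** Incidence and severity of adverse events is a declared secondary outcome, and safety is one of the two general objectives.

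- **Special-attention list (Protocol, Secondary outcomes).** It is introduced with "Due to the known effects of HCQ, special attention will be given to the incidence of the following adverse events". Its five items are cutaneous reaction, marrow suppression, severe hypoglycemia, proximal myopathy and suicidal risk. None concerns the eye.
- **Known reactions (same section).** Eye reactions appear as "10% ophthalmologic, dose dependent". All other organ classes are grouped as having no defined frequency.
- **Background.** "The main toxicity of HCQ, investigational drug in this trial; is retinopathy". The risk factors given are doses above 5 mg/kg/day, use beyond 10 years, kidney failure and tamoxifen.
- **Justification.** The dose of 200 mg/day with a 50 kg weight limit is one "which makes the risk of retinal toxicity minimal".
- **Exclusion criteria.** "History of retinopathy of any cause, and/or loss of central vision, loss of nocturnal visual acuity, blurred vision and alteration of color vision".
- **Follow-up (Gradation of adverse reactions; Tests to perform).** "Weekly researchers will ask all included subjects about the symptoms associated with COVID-19, as well as any possible adverse events". Participants are also told to report new symptoms, and adverse event surveillance is set for days 30 and 60. The scheduled tests are blood count, electrolytes, blood chemistry, hepatic profile and ECG.

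**The concern.** The list is presented as following from what is known about the drug, but it leaves out the toxicity that the protocol ranks first and the only reaction class to which it gives a frequency. Visual symptoms matter enough to bar entry, but no later contact mentions them.

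A general question about adverse events relies on the worker recognising a mild visual change as worth mentioning. If some do not, counts fall in both arms and a comparison showing no difference carries less information. The Experimental group section foresees offering the drug to both groups after an interim look, and possibly an open-label continuation, so the safety result may inform wider exposure.

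**Working it through.** The protocol gives no figure on this point that could be reproduced. The check compares sections, with some arithmetic for scale.

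1. **Is the omission real?** Yes. Background (main toxicity) and the reaction list (only stated frequency) both point to the eye, and the five-item list has no eye entry. This is an inconsistency on the face of the text.

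2. **Is there any eye-specific collection after entry?** No. Neither the evaluations under Gradation of adverse reactions nor those under Tests to perform include an eye test or a visual-symptom item. The day 30 and day 60 surveillance has no stated content.

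3. **Can a visual symptom be recorded at all?** Yes. The definition is "Adverse event: all medical events in the subjects included in the trial", so blurred vision qualifies. The weekly question, the self-report instruction and the two surveillance points are all routes by which it could be captured.

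4. **What would the stated frequency imply?** The final calculation gives 200 subjects per arm. The printed entry can be read as a range of 1% to 10%, or as list item 1 with a value of 10%. The upper figure is 10% either way.
   - Expected events = 200 × p. At p = 0.01 this is 2, and at p = 0.10 it is 20.
   - Chance of at least one event = 1 − (1 − p)^200. At p = 0.01 this is 1 − 0.99^200 = 0.866, and at p = 0.10 it exceeds 0.999.

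   These are general, dose-dependent frequencies. The protocol does not state them for a 60-day course at 200 mg/day.

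5. **How many would be recorded?** Recorded events = 200 × p × c, where c is the share of visual symptoms captured without a specific prompt. The documents give no value for c, so the shortfall cannot be calculated.

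6. **What would it do to the comparison?** The trial is double blind, so take the same c in both arms. The recorded risk difference is then c × (p1 − p0), and the ratio stays p1/p0. Incomplete capture shrinks the counts and the absolute difference and costs precision. It does not by itself favour either arm.

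7. **Does the low stated retinal risk conflict with the stated frequency?** At the weight limit the dose is 200/50 = 4.0 mg/kg/day, below the 5 mg/kg/day threshold in Background. The statement under Justification concerns the retina at this dose. The frequency under Secondary outcomes concerns all ophthalmologic reactions and is marked dose dependent. The two can both be true, but the text does not say whether the second applies here.

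**The case against.** The strongest reply is that the general system already covers the eye. Staff attend at least five days a week, are asked weekly about any adverse event, and are told to report anything new. Exact prompts usually sit in case report forms, which are not shown. The trial also avoids the risk factors that the protocol names: treatment lasts 60 days, and low weight, GFR of 30 or below, past tamoxifen and prior retinopathy are excluded. Nor is listing shown to improve collection, since the skin and myopathy items have no dedicated question either.

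Much of this stands, and it rules out several stronger readings that a reader might reach:

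- **That eye symptoms are never asked about after baseline.** The weekly question covers them. What is missing is a specific prompt.
- **That the trial would understate eye toxicity.** No capture rate is available, so only a possible under-count can be claimed.
- **That the retinal-risk and frequency statements contradict each other.** They concern different categories and settings.
- **That heart conduction is a parallel gap.** It is also off the list, but ECGs at baseline, 30 and 60 days are scheduled expressly to assess it.

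The reply does not explain the list itself. The protocol decided that the drug's known effects call for attention beyond the general question, then left out the effect it ranks first. If short, low-dose use is the reason, the text does not say so where it gives the frequency. The point about listing also shows that a line on the list is not enough without a question attached.

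**Conclusion.** The point holds as an inconsistency in the text and a modest gap in how one component of a secondary outcome is collected. The special-attention list omits the eye, and no eye-specific question is planned after the entry exclusion. Mild visual symptoms could be under-counted in both arms, by an amount the documents do not allow one to estimate.

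The figure of 2 to 20 treated subjects indicates scale only. It assumes that the general frequency carries over to this dose and duration, which the protocol does not state. The conclusion also assumes that the weekly question is open-ended as worded, with no visual prompt in forms that are not shown. The primary efficacy analysis is not affected.

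**What to change.** 1. Under Secondary outcomes, add ophthalmologic events to the special-attention list.
2. Under Gradation of adverse reactions and Tests to perform, state that the four visual symptoms in the exclusion criteria (central vision, night vision, blurring, colour vision) are asked about at the existing day 30 and day 60 contacts in both blinded arms. Compare newly reported symptoms by arm.
3. Beside the ophthalmologic frequency, state whether it is meant to apply at the trial's dose and duration, and make clear whether the figure is 10% or a range of 1% to 10%. Cross-refer to the retinal-risk statement under Justification.

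The cost is one line on the list, one clarifying sentence, and four questions at two contacts that already take place. No visit or eye examination is added. The small downside is some extra non-specific symptom reports, for which the placebo arm provides the control.
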